### Process evaluation analysis plan

Process evaluation analyses will be guided by IPEF. Quantitative process data will primarily take the form of simple descriptive statistics (e.g. proportions and percentages, means and standard deviations). Qualitative interview data will be transcribed verbatim and analysed using inductive thematic analysis procedures. Quantitative and qualitative data will be triangulated and systematically coded using the core theoretical frameworks to identify the change mechanisms of how leaders, workers and line managers translate the intervention materials into behaviour changes and the barriers and facilitators in doing so. This will provide us with valuable information on what works and under what context (e.g. readiness for change, culture) and how these lead to our intended outcomes.

#### Statistical analysis plan

A statistical analysis plan for the pilot will be finalised and agreed prior to analysis by the research team. The research outcome measures will be analysed and reported according to the Consolidation Standards of Reporting (CONSORT) statement for cluster RCTs. As this is a pilot study, we will examine the primary and secondary research outcomes to mimic practice for a full trial in addition to finalising the sample size for a definitive main trial. However, as this is a pilot study, no emphasis will be placed on the statistical significance of the effects.

The primary analyses will compare the number of calendar sick leave days (including non-working days) until the first day of partial or full return to work between arms post-12-month baseline data collection. Results will be treated as preliminary and interpreted with caution. Statistical analysis will be carried out on an intention-to-treat basis with missing outcome data being imputed using multiple imputation by chained equations (MICE) [63]. Effect sizes will be calculated but no emphasis will be put on the *p* values for any inferential statistical tests conducted. In order to inform the sample size calculation for a future trial, the present study analysis will carry out a preliminary examination of (1) between-group effect sizes and (2) the magnitude of the intra-cluster correlation coefficient (ICC) of the primary outcome using a mixed effects model.

In a future main trial, we will conduct a mixed effects Cox regression, in which censoring allows all data available at all time points to be used and account for missing data and clustering effect, to estimate a two-sided 95% confidence interval (CI) to show a reliable range for the true difference in the primary outcome (i.e. number of days taken to return to work [partial or full] between the intervention and control arms). Analysis of the main secondary outcome (number of days staying in work since RTW, with no exit or long-term sick leave re-occurrence) and other secondary outcomes (e.g. mental health, RTW self-efficacy, job crafting) 3, 6, 9 and 12 months will be analysed using a similar modelling strategy, but with the type of model adjusted for the nature of the outcome variable, and assumptions checked as far as possible to verify that the model types (e.g. mixed effects linear models, mixed effects, Cox regression models) appear correct. Additional analyses will focus on comparing the baseline characteristics of intervention and control arms as well as those lost to follow-up with those not lost to follow-up to assess for bias. As a future full trial analysis will control for appropriate demographic and work-related factors, exploratory analysis of pilot data will be used to identify which covariates should be included.

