An interplay of factors beyond the health condition is known to impact both return-to-work (RTW) outcomes (defined as the number of sick leave days until the first day of RTW with adjusted working hours or usual working hours) [15] and sustainable RTW outcomes (defined as number of days staying in work over a 6-month period after returning with no exit or long-term sick leave re-occurrence) [16]. Lower education and socio-economic status, older age, lower self-efficacy, poor line manager and/or co-worker support, inadequate work adjustments or lack of freedom to work flexibly (i.e. job crafting) and inadequate workplace return-to-work policies can all hamper sustainable return to work [16–19]. This has a detrimental impact on workers, leading to early retirement, job termination, unemployment [4] and reduced quality of life [9]. It also has a negative impact on employers through sick pay, staff turnover and productivity loss [9] and, more broadly, on society through health-related state benefits.

Evidence suggests that return-to-work outcomes in those with poor mental health are enhanced when symptom/problem-focused interventions (e.g. work-focused Cognitive Behavioural Therapy or solution-focused skills training ) are combined with elements of their workplace (e.g. contact with line manager during absence) [15, 16, 19]. A Cochrane review into mental health and long-term sick leave [19] found moderate evidence that a combination of work-directed and clinical interventions (such as psychological treatment) reduces sickness absence days within the first year of follow-up (SMD −0.25, 95% CI −0.38 to −0.12: 9 studies). Whilst this translates “to 0.5 fewer (95% CI −0.7 to −0.2) sick leave days in the past 2 weeks or 25 fewer days during 1 year (95% CI −37.5 to 11.8)” [19], the authors of the review propose that the integration of clinical and work-directed elements of an intervention is key to improving work outcomes.

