### Sample size

We will recruit eight cluster organisations [32] with ≥ 600 hundred workers (to minimise the risk of missing recruitment targets) into the feasibility pilot study (randomised in each arm) to calculate the target sample size for a definitive RCT. There is no formal requirement to conduct sample size calculations for pilot trials [33], but a sample of at least 100 participants is desirable [26]. Our target recruitment is 50 workers in the intervention arm and 50 workers in the control arm. We have no recruitment targets set for managers. Approximately 13 workers from each organisation will need to be recruited to reach our sample size. However, we aim to recruit 30 workers and 30 managers from each organisation to participate in the study to ensure that, even with a high possible level of attrition, 50 cases (workers) per arm are achieved [26, 33].

The target population is workers on long-term sick leave due to mental ill health or for a condition known to be associated with mental ill health [2, 12–14], who will be identified by their workplace between > 14 and < 42 days of their long-term sick leave and sent an invitation on behalf of the research team to participate in the study. The line manager of the individual worker on long-term sick leave will also be invited to participate in the study. Participation of the line manager is entirely voluntary, irrespective of whether their worker is taking part.

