#### Allocation to intervention

In this pilot RCT, organisations will be randomised using a 1:1 ratio. Randomisation to trial conditions (intervention versus control) will be carried out by assigning pre-prepared envelopes containing the allocation outcomes to the organisation. In each participating organisation, participants (i.e. senior leaders, managers and workers) will partake in the condition their organisation is allocated to and will therefore not be blinded in their group allocation. Prior to the intervention being deployed, an organisation-wide survey will take place to explore the ethos, culture and attitudes towards procedures for managing mental health and return to work in the organisation. All workers at the organisation will be eligible to participate in this.

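### For sizing the definitive trial the protocol names only the pilot's own effect size and ICC, and eight organisations estimate both too imprecisely for that purpose

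*Protocol article*

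**What the plan says.** In the protocol article, the Sample size section states the target: "We will recruit eight cluster organisations", and "Our target recruitment is 50 workers in the intervention arm and 50 workers in the control arm". The Allocation to intervention section adds that "organisations will be randomised using a 1:1 ratio", so there are four organisations per arm. About 13 workers per organisation are needed to reach the target, and the recruitment aim is 30.

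The same Sample size section gives the purpose of recruiting the clusters: "to calculate the target sample size for a definitive RCT". The Statistical analysis plan section says the research outcomes will be examined as in a full trial, "in addition to finalising the sample size for a definitive main trial". Later in that section, in a sentence framed as informing the future calculation, the inputs are named: "the present study analysis will carry out a preliminary examination of (1) between-group effect sizes and (2) the magnitude of the intra-cluster correlation coefficient", the ICC being that of the primary outcome.

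No other input is named for sizing. The Background cites a review estimate ("SMD −0.25, 95% CI −0.38 to −0.12: 9 studies"), but nothing links it to the main trial's size. The section also says that results will be treated as preliminary, and that p values will not be emphasised. The planned main-trial analysis is a mixed effects Cox regression of time to return to work.

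**The concern.** A pilot's observed effect is a poor basis for a target difference, for two reasons. It is not necessarily a difference worth detecting. It also carries a large chance error, and required size varies with one over the effect squared, so that error is magnified. In a cluster trial the precision of both the effect and the ICC is limited by the number of clusters, here eight, and extra workers within organisations only partly help.

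At stake is the size of the definitive trial. A pilot that happens to look favourable leads to a trial too small to detect a realistic effect. One that happens to look weak leads to an impractical size, and one with the wrong sign gives no meaningful size at all.

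**Working it through.** **Inputs from the protocol article.** 8 organisations, 1:1 (4 per arm); 50 workers per arm; about 13 workers per organisation needed, 30 aimed for; two-sided 95% interval for the main trial; review SMD of 0.25 in size (Background).

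**Assumptions.** ICC of 0.01, 0.05 or 0.10 (none is given); 80% power (none is given); a true SMD of 0.25, and 13 workers per organisation in the main trial, for illustration; equal cluster sizes and no attrition. Losses would widen the intervals.

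**1. The plan's own figure.** 100 / 8 = 12.5, rounded up to 13 per organisation (8 × 13 = 104). It reproduces.

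**2. Precision of the pilot effect.** With m workers per organisation and n = 4m per arm, the design effect is DE = 1 + (m − 1) × ICC and SE = √(2/n × DE). The half-width is t × SE, with t = 2.447 on 8 − 2 = 6 df. The chance of the wrong sign when the true SMD is 0.25 is Φ(−0.25/SE).

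Example, m = 13 and ICC 0.05: DE = 1 + 12 × 0.05 = 1.6; SE = √(2/52 × 1.6) = 0.248; half-width = 2.447 × 0.248 = 0.61; Φ(−0.25/0.248) = 16%.

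| m | ICC | DE | SE | 95% half-width | Wrong sign |
|---|---|---|---|---|---|
| 13 | 0.01 | 1.12 | 0.208 | 0.51 | 11% |
| 13 | 0.05 | 1.60 | 0.248 | 0.61 | 16% |
| 13 | 0.10 | 2.20 | 0.291 | 0.71 | 20% |
| 30 | 0.01 | 1.29 | 0.147 | 0.36 | 4% |
| 30 | 0.05 | 2.45 | 0.202 | 0.49 | 11% |
| 30 | 0.10 | 3.90 | 0.255 | 0.62 | 16% |

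Every half-width exceeds the assumed effect of 0.25.

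**3. Precision of the ICC.** From a one-way analysis of variance within arms, F = (1 + (m − 1) × ICC)/(1 − ICC) on 6 and 8(m − 1) df. Dividing F by the 97.5% and 2.5% points of the F distribution gives limits F*, and each ICC limit is (F* − 1)/(F* + m − 1).

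- m = 13, observed ICC 0.05: F = 1.6/0.95 = 1.684 on 6 and 96 df. F* = 1.684/2.543 = 0.662 and 1.684/0.2033 = 8.283. The limits are −0.027 and 0.359, or about 0 to 0.36. At 13 per organisation that is a design effect of 1.0 to 5.3.
- m = 30, observed ICC 0.05: F = 2.45/0.95 = 2.579 on 6 and 232 df. The limits are 0.002 and 0.278.

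**4. What this does to a sample size.** Before clustering, n per arm = 2 × (1.96 + 0.8416)²/d². This is 251 at d = 0.25 and 63 at d = 0.50. At m = 13 and ICC 0.05, an estimate of 0.50 or more has probability 1 − Φ(0.25/0.248) = 16% when the truth is 0.25.

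In 50,000 simulated pilots (8 × 13, true SMD 0.25, true ICC 0.05), each pilot's own effect and ICC were put into this formula with the design effect. The correct total is 4 × (1.96 + 0.8416)²/0.25² × 1.6 = about 804. The quartiles of the resulting total were 266 and 2,994, and 36% of pilots gave less than half of 804. This simulation takes the point estimates at face value, so it shows the risk of that use and is not a prediction of what the investigators will do.

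**5. Fixing the effect alone.** With d held at 0.25 and only the ICC taken from the pilot, the central 95% range of the total was about 502 to 1,701. The ICC therefore needs a range too.

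**The case against.** The strongest reply is that the protocol does not commit to putting these estimates into a formula. The two phrases about calculating and finalising the size name no inputs, and the sentence that names the inputs describes them as informing the calculation through a preliminary look. Results are to be read with caution, the main trial will have its own protocol, and estimating an ICC in a pilot is routine. This stands in part: a reader might infer that the point estimates will be used mechanically and outside values excluded, and the text does not say so. But the cautions concern interpretation and p values. They do not supply another target difference, and none is named anywhere for sizing.

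A reader might also infer that an unfavourable pilot effect would discard the intervention. The document does not support that. The stop-go criteria under Study outcome and data analysis are recruitment, retention, intervention completion and usability, and the effect estimate is not among them.

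It is also fair to say that 13 per organisation is the minimum and that the figures depend on an assumed ICC. That is why both cluster sizes and a range of ICCs are shown. With 30 per organisation the estimates improve but remain too imprecise.

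Finally, the review SMD cannot simply be adopted as the target. It concerns sickness absence days in the first year of follow-up, whereas the outcome here is time to first return, to be analysed by Cox regression. It serves above only as an illustration.

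The plan that "exploratory analysis of pilot data will be used to identify which covariates should be included" is a minor matter, described as exploratory, and is not part of this point.

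**Conclusion.** The point holds as a badly chosen basis for sizing, stated in the protocol itself. The only named inputs for the definitive sample size are two pilot estimates that eight organisations cannot deliver with useful precision. Over the assumed ICC range the conclusion is the same at 13 and at 30 workers per organisation, because the 6 between-cluster degrees of freedom do not change. The exact percentages rest on the assumed ICCs, a true SMD of 0.25 and equal clusters. The SMD scale stands in for the planned Cox analysis, where the number of clusters is the same limit. The consequence is confined to the size of the main trial. It does not extend to the decision whether to proceed, and it is a risk created by the wording, not proof that the estimates will be misused.

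**What to change.** In the Sample size and Statistical analysis plan sections, state that:

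- the definitive trial will be sized on a target difference justified independently of the pilot estimate and expressed on the scale of the planned primary analysis (time to return to work, Cox model);
- the calculation will be shown over a range of ICCs that takes account of the pilot's confidence interval and of outside values;
- the pilot will supply the return-to-work proportion or SD, attrition, uptake and variation in cluster size;
- the pilot effect will be reported with a small-sample (6 df) interval and will not be used as the target difference.

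The cost is wording, plus the work of justifying a target difference. No data collection changes. The downside is that the projected main trial may be larger than a favourable pilot would suggest.

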## Background

Long-term sickness absence costs UK businesses approximately £7 billion per annum [1]. Most long-term sickness absences are attributed to common mental health conditions (e.g. stress, depression, anxiety) [2], which are also highly prevalent in people with acute (e.g. cardio-respiratory, stroke) or musculoskeletal health conditions [2, 3]. Keeping people at work following long-term sick leave is a societal challenge because long-term sick leave is strongly linked to disability pension, unemployment and job termination [4]. With an ageing workforce, the risk of ill-health and life-long disability is also rising [5], bringing further societal challenges. Moreover, the coronavirus SARS-2 (COVID-19) pandemic brings unprecedented difficulties to people’s mental health [6], with global prevalence estimates of mental health issues among the general population amid the pandemic reported to be 28.0% for depression; 26.9% for anxiety and 36.5% for stress symptoms [7]. Furthermore, the prevalence of long-term fatigue, cognitive problems and anxiety and depressive symptoms is evident months after infection [8].

The need for practical measures to enable employer-led sustainable return to work has received considerable attention over the last decade [9]. In 2019, the National Institute for Health and Care Excellence (NICE) [1] highlighted a UK research gap in effective and cost-effective interventions to reduce long-term sickness absence (i.e. those occurring for >14 consecutive days) and supportive return to work particularly for common mental health conditions. Long-term sickness absence not only has a negative impact on employers but also has a significantly detrimental effect on workers [10].

For people returning to work following long-term sick leave, good work can be therapeutic by minimising the harmful effects of long-term sickness absence, loss of work productivity, and the risk of long-term incapacity [11]. However, facilitating a return to work and enabling people to stay at work is challenging, especially where a common mental health condition is the main reason for long-term sick leave or is present for another reason [12–14].

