#### Primary outcome measures (phases 2 and 3)

The primary research outcome of the study, the total number of days on sick leave, will be collected for control and intervention participants. The number of sick leave days will be calculated from the first day of sick leave recorded on a participant’s ‘fit note’ (obtained from their general practitioner or medical doctor and submitted to their employer), until their first day back at work using self-report data from the participant. Sick leave days are counted in calendar days and not just the days a person typically works on. For example, weekends and non-working days are counted as part of sick days. The information will be collected from participants via text messaging at monthly intervals as well as asked in the baseline questionnaire, and in their 3-, 6-, 9- and 12-month follow-up questionnaires. Participants will be asked whether they have returned to work and, if so, what was the date of their first day back at work. If they have not returned to work during their participation, then the last point this question will be asked will be at their final data collection point at 12 months (see Table 2). Self-report of sickness absence has been shown to be adequately reliable when compared with organisational records [43, 44].

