#### Secondary outcome measures for worker participants on long-term sick leave

##### The number of days staying at work over a 6-month period with no exit or long-term sick leave re-occurrence (main trial secondary outcome)

Once a participant is back at work, we will collect regular data from them (through monthly texts) on any subsequent sick leave taken or leaving the organisation over a 6-month period.

The following secondary outcome measures will be collected via questionnaires at baseline, 3, 6, 9 and 12 months from participant workers.

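### The pilot's days-to-return outcome makes no provision for workers who leave before returning, and the imputation rule does not exempt them

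*Protocol article*

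**What the plan says.** All references are to the Protocol article.

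- **Outcome.** Under Primary outcome measures (phases 2 and 3), sick leave days run from the first day on the fit note "until their first day back at work using self-report data from the participant". Participants are asked whether they have returned and, if so, on what date, by monthly text and in the questionnaires up to 12 months.
- **Exit.** It appears under the main secondary outcome. Once a participant is back, monthly texts ask about "any subsequent sick leave taken or leaving the organisation over a 6-month period".
- **Pilot analysis.** Under Statistical analysis plan, the main comparison of the arms is in days to partial or full return, by intention to treat. The rule for incomplete data is "missing outcome data being imputed using multiple imputation by chained equations (MICE"). The same section uses a mixed effects model to obtain the effect size and intra-cluster correlation (ICC) for the future sample size, and says "we will examine the primary and secondary research outcomes to mimic practice for a full trial".
- **Main trial.** The Cox model with mixed effects is reserved for a later, definitive trial. The article describes it as a model "in which censoring allows all data available at all time points to be used and account for missing data and clustering effect".
- **Background.** The article states that "long-term sick leave is strongly linked to disability pension, unemployment and job termination". Discussion and conclusion adds that return to employment becomes unlikely once absence has lasted six months.

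**The concern.** A worker who resigns, is dismissed or retires on ill-health grounds while still on sick leave has no first day back to report. That is a definite outcome, and on the article's own account a foreseeable one. It differs from a questionnaire that was not returned. After return, exit counts against the worker in the main secondary outcome; before return it has no status.

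Two quantities are at stake: the effect size and the ICC of days to return, both of which the pilot is meant to hand to the main trial. If leavers fall under the general imputation rule, each receives a return time drawn from a model fitted largely to people who did return. The worst outcomes would then look like ordinary ones. A benefit of the intervention in preventing job loss, or a harm in hastening it, would be removed from the comparison. The pilot would also end without the exit rate that the main trial needs for its own planning.

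**Working it through.** **1. What the described data can distinguish.** Four kinds of worker exist at 12 months:

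| Status | What the described questions yield |
|---|---|
| Returned | A return date |
| Still on sick leave, responding | Not returned |
| Left before returning | Not returned if still responding, nothing if not |
| Non-responder | Nothing |

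The third row has no record of its own. A leaver looks like someone still absent or like a non-responder. Table 2 agrees: before return it schedules days off sick but no exit item, and intention to quit is asked only after return. The section on trial management says participation is not shared with the organisation, so the monthly meetings with human resources are not an obvious way to learn of individual exits.

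**2. Which rule then applies.** The only device named for incomplete pilot outcomes is multiple imputation, with no exception. The only one named for the main trial is censoring.

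**3. Size in the pilot.** The article gives no exit rate, so everything here is assumed. At the target of 50 workers per arm, exit of 2% to 15% is 50 × 0.02 = 1 to 50 × 0.15 = 7.5 workers per arm.

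Let p be the proportion leaving and m their mean imputed days. If leavers would otherwise count as not returned for about 365 days, imputation lowers the arm mean by p × (365 − m).

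- p = 0.02, m = 150: 0.02 × 215 = 4.3 days.
- p = 0.15, m = 90: 0.15 × 275 = 41.3 days.

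If p and m are equal in both arms, the shift cancels in the raw difference, though the spread still changes. If exit differs by 5 points between arms and m is the same, imputation removes 0.05 × 215 = 10.8 to 0.05 × 275 = 13.8 days from the difference. For scale, the review cited in the Background reports 25 fewer days over a year.

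**4. What censoring at exit does.** Take constant hazards over 12 months, with R the true proportion returning and E the proportion leaving first. Then λ = −ln(1 − R − E)/12, the return hazard is λ × R/(R + E), and one minus Kaplan-Meier is 1 − exp(−12 × return hazard).

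For R = 0.70 and E = 0.10: λ = 0.1341, return hazard = 0.1174, result 75.5%, which is 5.5 points too high. Across E of 2% to 15%, the excess is:

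| R | Excess (points) |
|---|---|
| 60% | 0.8 to 7.0 |
| 70% | 1.0 to 9.0 |
| 80% | 1.2 to 12.0 |

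Now give both arms a return hazard of 0.12 per month, with exit hazards of 0.01 and 0.03:

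- (0.12/0.13) × (1 − exp(−1.56)) = 72.9% return.
- (0.12/0.15) × (1 − exp(−1.80)) = 66.8% return.

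The cause-specific hazard ratio is 1 in this case. It is correct, but it does not show the 6.1-point difference in return. The article plans no Kaplan-Meier return proportion, so step 4 bears on how a main-trial Cox result should be read and does not measure an error in a planned figure.

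**The case against.** Several points on the other side stand.

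- **Silence is not a rule.** A reader might infer that the plan treats leavers as missing or censored. It does not say so; it does not mention them. A coding rule could properly sit in the statistical analysis plan, which the article says is still to be finalised. However, an analysis plan cannot recover an event that was never recorded, and the article does describe which questions are asked and when.
- **The questionnaires are not reproduced.** The article describes exit questions after return; it does not state that none is asked before. The finding rests on the collection as described.
- **The Cox sentence belongs to a future trial.** A reader might infer that censoring assumes a return date for leavers. It assigns none, and a Cox model censored at exit gives a valid cause-specific hazard ratio. The fault would lie in reading it as a difference in days to return, which is how the article describes the estimate. Only imputation would create a return time, and only the imputation sentence governs the pilot.
- **Leavers may work again.** It is tempting to say they will never return. The outcome wording does not restrict return to the same employer, and some may start elsewhere within 12 months.
- **Limited consequence.** Feasibility is the pilot's primary outcome, none of the four stop-go criteria uses days to return, results are to be treated as preliminary, and p values carry no emphasis. A comparison of those lost to follow-up with those retained is also planned, but it cannot isolate leavers who were never identified.

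**Conclusion.** The point holds as a gap. The pilot's days-to-return outcome is undefined for workers who leave before returning, exit is described as collected only after return, and the imputation rule makes no exception. Followed as written, leavers could receive imputed return times that carry over into the effect size and ICC used for main-trial planning.

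The size is unknown. The shifts of 4.3 to 41.3 days in an arm mean, and the 1 to 12 point overstatement of return, rest entirely on assumed exit rates, return proportions and imputed times. They show that the matter is not negligible if exits are common, and they predict nothing about this trial. Severity is low to moderate. The documents do not support a claim that the pilot's feasibility decision is affected or that the Cox model itself is invalid.

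**What to change.** 1. In the monthly text and the follow-up questionnaires, add a dated answer option: left the organisation before returning. State whether starting work with another employer counts as return.
2. In the pilot analysis, exclude recorded leavers from imputation of a return date. In the days measure, count them as not returned up to 12 months. Keep imputation for true non-response.
3. Report exit before return by arm as a competing event, with the cumulative incidence of return and of exit.
4. For the future main trial, label the Cox estimate a cause-specific hazard ratio and do not describe it as a difference in days to return.

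The cost is one more answer option in messages already being sent, one additional analysis, and two event types to report instead of one. In exchange, the pilot yields an exit rate for main-trial planning.

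### Secondary scores measured at baseline (PHQ-9, GAD-7, burnout, EuroQol, RTW self-efficacy) should be analysed with their own baseline value as a prespecified covariate; the stated covariate rule does not secure this

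*Protocol article*

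**What the plan says.** **Measurement.** Before listing the worker scales, the article states: "The following secondary outcome measures will be collected via questionnaires at baseline, 3, 6, 9 and 12 months from participant workers". Table 2 marks mental health, quality of life, RTW self-efficacy, and workplace support and communication at baseline and at all four follow-ups. The section on mental health and quality of life measures shows that PHQ-9, GAD-7, the burnout exhaustion scale and EuroQol are the instruments concerned. Readiness to stay at work, job autonomy, job crafting, and job satisfaction with intention to quit are collected only after return and have no baseline cell.

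**Analysis.** The Statistical analysis plan section says that "other secondary outcomes (e.g. mental health, RTW self-efficacy, job crafting) 3, 6, 9 and 12 months will be analysed using a similar modelling strategy", with the model type suited to the outcome. On covariates it says: "As a future full trial analysis will control for appropriate demographic and work-related factors, exploratory analysis of pilot data will be used to identify which" terms to include. Its other stated use of baseline data is descriptive: "Additional analyses will focus on comparing the baseline characteristics of intervention and control arms", together with a comparison of those lost to follow-up with those retained.

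**Link to the pilot.** The same section says of the pilot that "we will examine the primary and secondary research outcomes to mimic practice for a full trial". It also says that effect sizes will be calculated, and that a separate statistical analysis plan will be finalised before analysis. That plan is not shown.

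**The concern.** The baseline value of a repeated score is usually its strongest single predictor, and here it is already being collected. The article nevertheless describes the covariates by a class to which four of the five scores clearly do not belong, and it makes the choice within that class depend on the pilot data. An analysis plan that follows this wording could leave out the baseline PHQ-9 score from the PHQ-9 model, or include it only if an exploratory search happens to favour it.

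Tabulating baseline differences between arms shows an imbalance but does not take it out of the estimate. With four organisations per arm, randomisation cannot be relied on to balance these scores. At stake are the secondary effect sizes that the pilot will report, the width of their intervals, and the model form that the pilot hands on to the main trial.

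**Working it through.** **Inputs from the article.** Eight organisations (Sample size), allocated 1:1 by organisation (Allocation to intervention), so 4 v 4; target of 50 workers per arm (Sample size). The article's own figure of about 13 workers per organisation reproduces: 100 / 8 = 12.5, rounded up to 13 (8 × 13 = 104).

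**Assumptions, because the article gives no figure.** ICC of a secondary score: 0.01, 0.05 or 0.10. Correlation r between a baseline score and its follow-up score: 0.3, 0.5 or 0.7, taken to be the same at worker and organisation level.

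**Step 1: chance baseline difference between arms, in SD units.** With m = 12.5 per organisation, DE = 1 + (m − 1) × ICC and SE = √(2 × DE / 50).
- ICC 0.01: DE = 1 + 11.5 × 0.01 = 1.115; SE = √0.0446 = 0.211
- ICC 0.05: DE = 1.575; SE = √0.0630 = 0.251
- ICC 0.10: DE = 2.150; SE = √0.0860 = 0.293

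The chance that the arms differ by more than 0.25 SD is 2 × (1 − Φ(0.25 / SE)): 24%, 32% and 39% respectively. The 0.25 is only a yardstick. The Background cites a standardised difference of that size, but for sickness absence days.

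**Step 2: what passes into an unadjusted follow-up comparison.** A baseline difference d shifts the follow-up difference by r × d. For d = 0.25 the shift is 0.075, 0.125 or 0.175 SD at r = 0.3, 0.5 or 0.7. Over repeated randomisations this component has SD r × SE, from 0.3 × 0.211 = 0.06 to 0.7 × 0.293 = 0.21.

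**Step 3: precision.** The unadjusted follow-up difference has the same SE as in Step 1. Adjustment multiplies its variance by about 1 − r²: 0.91, 0.75 or 0.51. It therefore removes 9%, 25% or 49% of the unadjusted variance. The adjusted SE is SE × √(1 − r²).

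| ICC | Unadjusted SE | r = 0.3 | r = 0.5 | r = 0.7 |
|---|---|---|---|---|
| 0.01 | 0.211 | 0.201 | 0.183 | 0.151 |
| 0.05 | 0.251 | 0.239 | 0.217 | 0.179 |
| 0.10 | 0.293 | 0.280 | 0.254 | 0.209 |

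**Step 4: check by simulation.** Eight clusters of 13, 4,000 runs per setting, no true effect, chance imbalance only, with adjustment by least squares on the baseline score. At ICC 0.05 and r = 0.5 the empirical SD of the estimate was 0.250 unadjusted and 0.216 adjusted, against 0.251 and 0.217 by formula. The mean error was within 0.005 SD of zero in every setting, with and without adjustment.

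**The case against.** The strongest reply is that the article is silent on baseline scores and does not exclude them. It closes no covariate list, it names model families that can readily take a baseline term, and it promises a separate analysis plan, where covariate terms for secondary outcomes normally sit. The covariate sentence also concerns the future trial, and no covariate set yet exists for the pilot to copy. Most of this stands. A reader might infer that the plan restricts adjustment and bars baseline scores; the text does not say so. What remains is that the article does not simply defer the matter: it names a class of covariates and a data-driven way of choosing among them, and it asks the pilot to rehearse the full-trial analysis. That rule is stated, and it fits these outcomes poorly.

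The second reply concerns consequence. Feasibility is judged on recruitment, retention, completion and usability, none of which uses a secondary score. The primary research outcome, days to RTW, has no baseline score of this kind. The pilot also sets little store by significance tests. All of this stands and limits the weight of the point, but effect sizes will still be reported, and these are what an imbalance shifts.

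The third reply is that adjusting every score for its baseline could do harm. In Table 2 allocation precedes baseline, and the leader e-learning sits in the baseline column. Baseline workplace support, communication and manager confidence may therefore already reflect the intervention, and adjusting for them could remove part of its effect. This stands and narrows the remedy.

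**Conclusion.** The point holds as a modest, inexpensive improvement to a stated rule. Followed as written, the covariate rule omits the baseline values of PHQ-9, GAD-7, burnout and EuroQol, and arguably RTW self-efficacy, or leaves them to selection on the pilot data. At the target of 50 per arm, the price is a chance baseline difference with SE 0.21 to 0.29 SD passing partly into the secondary effect sizes, and 9% to 49% of the unadjusted variance that adjustment could have removed. These figures rest on the assumed ICC and r; the gain is small at r = 0.3.

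Three stronger readings are not supported.
- **Systematic bias.** A reader might infer that the unadjusted effects are biased. Under chance imbalance the mean error is about zero, so the loss is one of precision. Workers consent after allocation and without blinding, so differential recruitment is possible, and the article lists selection bias as something to assess. Nothing in it shows that it will occur, and adjustment would not remove all of it.
- **Power of the definitive trial.** A reader might carry the variance reduction over to the main trial's power. That trial's primary outcome is time to RTW, to which this adjustment does not apply, and the pilot has no formal power calculation.
- **Every baseline score.** A reader might extend the adjustment to all repeated scales. Workplace support and RTW self-efficacy can be read as work-related, and the baselines of support, communication and the manager scores may follow the Phase 1 e-learning.

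**What to change.** Add to the Statistical analysis plan section that PHQ-9, GAD-7, burnout, EuroQol and RTW self-efficacy are each analysed with their own baseline score as a prespecified covariate in the mixed model, in the pilot and in the main trial. The exploratory search then concerns additional covariates only. Include missing baseline scores in the multiple imputation already planned.

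For workplace support and communication and for the manager scores, do not make baseline adjustment mandatory; report it as a sensitivity analysis. Leave the scales collected only after return to work as they stand.

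The cost is a sentence or two of analysis wording and one more worker-level parameter per model, with no new data.
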